## Methods/design

We designed a multicenter randomised controlled cost-effectiveness trial on the treatment of low-grade spondylolytic spondylolisthesis in which two surgical techniques are compared in a parallel group design. The primary outcome measure is the Roland Disability Questionnaire (RDQ) for sciatica. The follow-up period will last 2 years (with extension to 5 years). In order to collect enough patients, a multicenter design is necessary. The study protocol is approved in all participating hospitals by the Medical Ethics Committee.

We hypothesise that nerve root decompression according to Gill is more (cost-)effective on the short term (12 weeks) and equally (cost-)effective on the long term (2 years). Equal effectiveness is defined as maximal 4 points difference on the RDQ score between decompression and instrumented fusion. Moreover, we will identify subgroup of patients who may benefit more of one of the allocated treatments.

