### Sample size

The sample size is calculated on the basis of the RDQ both at both short term and long term follow-up. A difference in effectiveness is considered clinically relevant whenever patients with nerve root decompression alone will obtain at least 20% difference in RDQ score. Instrumented spondylodesis is assumed to result in at least 60% good outcome at 12 weeks. This means that 80% of the patients treated with nerve root decompression alone should have good results in order to proof superiority of Gill's procedure. Treatment is considered to be justified in case of improvement of at least 7 points on the RDQ score; 20% difference corresponds to 8.4 points improvement on in the RDQ score. With a power of 90% and a two-tailed significance level of 0.05, 220 patients with symptomatic spondylolytic spondylolisthesis grade I and II are needed (110 patients in both treatment groups, including 10% loss to follow-up). The numbers used for this sample size calculation are retrieved from the 1 and 5-years results of the Maine Lumbar Spine Study [38,39].

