### Statistical analysis

Baseline comparability will be analysed by descriptive statistics to determine whether randomisation was successful. Whenever necessary to remove residual confounding or simply in order to increase power, adjustments for baseline variables will be performed in the analyses. Differences in outcome measures between both groups, together with 95% confidence intervals, will be calculated. We stipulate in advance that we will also analyze a model containing the interaction of follow-up time and randomisation group; if the latter is significant at the 5% level, the conclusion of "unequality of treatments" follows; if the latter is non-significant, the treatment effect will be calculated on the basis of a model without group*time interaction. All data will be analysed according to the "intention-to-treat principle". We state a priori that we will perform as a subgroup analysis, the evaluation of the interaction between the treatment allocation and both the grading of the disease (grade I versus grade II spondylolisthesis) as well as the localisation of nerve root compression (underneath the pseudo-joint or between pedicle and slipped disc). We will conclude that the treatment effect depends on the value of those variables if the interaction is significant at the 5% level. If the interaction is non-significant, we will quantify the main effect of these variables in the usual way. In addition, explorative subgroup analyses will be performed, based on the interaction between the randomization variable and various different baseline variables (table 3). Data will be stored via the internet-based secure data management system "ProMISe" of the department of Medical Statistics and Bioinformatics. The analyses will be carried out using appropriate statistical software (e.g. SPSS).

**Table 3 T3:** Selected prognostic variables for subgroup analysis

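### The a priori subgroup rule lets p < 0.05 decide what is quantified and, when the interaction is non-significant, turns to the variable's main effect, in a trial sized only for the overall comparison

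*Protocol article*

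**What the plan says.** The protocol article (Statistical analysis) names two variables whose interaction with treatment is tested a priori: slip grade (I or II) and where the nerve root is compressed. The rule has two branches.

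- Significant: "We will conclude that the treatment effect depends on the value of those variables if the interaction is significant at the 5% level".
- Not significant: "If the interaction is non-significant, we will quantify the main effect of these variables in the usual way".

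The Methods/design section makes subgroup identification an aim: "Moreover, we will identify subgroup of patients who may benefit more of one of the allocated treatments". The end of the Background says much the same, as a second purpose.

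The Sample size section addresses only the comparison of the two arms as a whole: "Instrumented spondylodesis is assumed to result in at least 60% good outcome at 12 weeks", against which "80% of the patients treated with nerve root decompression alone should have good results". The number is "110 patients in both treatment groups, including 10% loss to follow-up". No power, effect size or subgroup split is given for any interaction.

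**The concern.** The p-value of the interaction decides which quantity is estimated next. When the test is not significant, the quantity named is the main effect of grade or of compression site. That is a prognostic contrast: it says whether, say, grade II patients do worse than grade I patients whichever operation they have. It says nothing about whether the difference between the operations varies with grade. The non-significant branch therefore leaves the subgroup aim for a different question.

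This would matter less if the test were likely to detect a modification worth knowing about. The trial was sized for the overall difference, and an interaction is estimated much less precisely than an overall effect. If the rule is followed and nothing is added, readers could not tell an absence of effect modification from a shortage of information.

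**Working it through.** **Inputs from the protocol article.** Good outcome 60% versus 80%, two-sided 5%, 90% power, 110 per arm including 10% loss (Sample size). Evaluable: 110 × 0.9 = 99 per arm. Equal effectiveness is a difference of at most 4 RDQ points (Methods/design).

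**Assumed, because not stated.** Subgroup split 50:50, 70:30 or 80:20; RDQ SD 5 to 7; interaction sizes borrowed from the overall comparison (20 percentage points, 4 RDQ points).

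**1. The plan's own figure.** With pooled variance,

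n per arm = [1.96·√(2·0.7·0.3) + 1.2816·√(0.6·0.4 + 0.8·0.2)]² / 0.20² = (1.270 + 0.811)² / 0.04 ≈ 108.2, so 109.

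The stated 110 per arm is therefore the size for the overall difference, before any loss. At 99 evaluable per arm the power for that difference is 87.2%. That shortfall is a separate matter. Here the result shows that nothing in the number was set aside for interactions.

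**2. Precision of an interaction.** With equal variances, 1:1 allocation and a share f of patients in one subgroup,

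SE(interaction) = SE(overall) / √(f(1−f)),

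which is 2.0, 2.18 and 2.5 times the overall SE for f = 0.5, 0.7 and 0.8.

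Miss rate = 1 − [Φ(θ/SE − 1.96) + Φ(−θ/SE − 1.96)].

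**3. A 20-point interaction in good outcome.** Larger subgroup: 80% on decompression alone versus 60% on fusion. Other subgroup: 60% versus 60%. SE is the square root of the sum of p(1−p)/n over the four cells. At 50:50 each cell has 49.5 patients: √[(0.16 + 3·0.24)/49.5] = 0.133.

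| Split | SE | 0.20/SE | Missed |
|---|---|---|---|
| 50:50 | 0.133 | 1.50 | 67.7% |
| 70:30 | 0.148 | 1.35 | 72.8% |
| 80:20 | 0.171 | 1.17 | 78.5% |

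With all 110 per arm evaluable the range is about 65% to 77%. A 40-point interaction (80% versus 40% on decompression, 60% on fusion in both subgroups) is missed in 15% to 35% at 99 per arm.

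**4. A 4-point RDQ interaction.** SE = SD·√(2/99)/√(f(1−f)), one unadjusted time point. For SD 6 at 50:50: 6 × 0.1421/0.5 = 1.706 and 4/1.706 = 2.345, so 35% are missed.

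| SD | 50:50 | 70:30 | 80:20 |
|---|---|---|---|
| 5 | 19.6% | 26.8% | 38.5% |
| 6 | 35.0% | 42.5% | 53.3% |
| 7 | 48.0% | 54.7% | 63.7% |

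**5. What a non-significant result leaves open.** At SD 6 the 95% half-width for the interaction is 3.34 points at 50:50 and 4.18 at 80:20. At 50:50, any non-significant estimate larger than 4 − 3.34 = 0.66 points in either direction has an interval that reaches beyond 4 points. At 80:20, even an estimate of zero does.

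**The case against.** Several points on the other side are sound.

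- **What the text leaves unsaid.** A reader might infer that the main effect is all that will be reported, or that p > 0.05 will be taken to show a uniform treatment effect. The article says neither. It states what will be quantified, without excluding other estimates. The only explicit conclusion is attached to a significant result. It also promises group differences with 95% confidence intervals, although it does not extend this to interactions or subgroups.
- **Borrowed benchmarks.** The 20-point difference and the 4-point limit belong to the overall comparison. Neither is offered as a relevant difference between subgroup effects.
- **Unadjusted figures.** The plan allows baseline adjustment to gain power, and RDQ is measured repeatedly. With an assumed baseline correlation of 0.5, SD 6 becomes 6·√(1 − 0.25) = 5.2, and the 50:50 miss rate falls from 35% to about 23%.
- **Otherwise good practice.** Only two modifiers are named a priori, they are tested by formal interaction, and the further subgroup analyses are called explorative. The subgroup aim comes second, and the primary comparison is untouched.

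It could also be said that a condensed article leaves reporting detail to the full protocol or analysis plan. That does not dispose of the point, because the rule itself is printed as an advance commitment and its second branch names the wrong quantity for the aim. The neighbouring rule for group by time points the same way: when that interaction is non-significant, the term is removed from the model.

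**Conclusion.** The point holds as a defect in a stated rule. A significance test selects what is quantified, and the non-significant branch turns to a prognostic effect that cannot answer who benefits more from which operation. Because the trial was sized only for the overall comparison, a non-significant interaction is weak evidence of a uniform effect.

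The size is conditional. At 99 evaluable per arm and splits from 50:50 to 80:20, about 68% to 79% of trials miss a 20-percentage-point interaction. About 20% to 64% miss a 4-point RDQ interaction for SD 5 to 7, unadjusted and at one time point.

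A reader might infer that the test will usually miss a relevant interaction, or attach a single miss rate to it. The documents do not support that. They define no relevant interaction and give no SD or split. In five of the six RDQ scenarios at SD 5 and 6 the test detects 4 points more often than not. The primary analysis and its conclusion are unaffected, so this is a cheap improvement to a secondary aim.

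**What to change.** Replace the sentence for the non-significant branch with wording such as:

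> For slip grade and site of compression we will report, whatever the interaction p-value, the interaction estimate with its 95% confidence interval and the treatment difference with its 95% confidence interval within each subgroup, all from the model that keeps the interaction term. A non-significant interaction will not be taken as evidence that the treatment effect is the same across subgroups. The main effect of each variable will be presented as prognostic information only.

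The cost is one change of wording and a few extra estimates from a model already planned, with no added patients or data. The downside is that wide subgroup intervals will be on display.

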***Demographic variables:***
• Women versus men
• Age < 40 years versus > 40 years
• Smoking versus non-smoking
***Anamnestic and neurological variables:***
• Influence of back extension versus no influence
• Predominant low back pain versus leg pain
• Quetelet index < 25 versus > 25
***Radiological variables:***
• Low disc height versus high disc height
• Nerve root compression underneath pseudojoint versus nerve root compression between pedicle and slipped disc
• Grade I versus grade II spondylolytic spondylolisthesis
• Small cross section versus large cross section of neuroforamen
• Low grade versus high grade epidural fat

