#### 8) Radiological examinations

Preoperatively, all patient will undergo dynamic radiographs, CT and MRI. The exact slip percentage and the slip angle will be measured on plain X-ray. The localisation of nerve root compression (lateral recess, parapedicular underneath pseudojoint, neuroforamen between pedicle or slipped disc, or combination) and the amount of nerve root compression will be quantified on MRI. We have developed the following grading scale based on the epidural fat reduction in the neuroforamen: 0–25% fat reduction (grade 1), 25–50% fat reduction (grade 2), 50–75% fat reduction (grade 3), and more than 75% fat reduction (grade 4). In addition, the diameter of the neuroforamen will be measured on sagittal CT reconstructions. During the follow-up, dynamic X-rays, CT and MRI will be repeated (table 2).

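### Table 3's explorative interactions use two-group splits that omit boundary values and discard information, and two imaging labels do not match the measurement section

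*Protocol article*

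**What the plan says.** The Statistical analysis section names two a priori subgroup variables, slip grade and site of nerve root compression. It then announces explorative subgroup analyses based on interactions between randomised group and the baseline variables in Table 3.

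Table 3 shows several measured quantities as two groups:

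- Demographic variables: "Age < 40 years versus > 40 years".
- Anamnestic and neurological variables: Quetelet index below 25 against above 25.
- Radiological variables: "Low disc height versus high disc height", "Small cross section versus large cross section of neuroforamen" and "Low grade versus high grade epidural fat".

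The measurements are described under Secondary outcome measures, 8) Radiological examinations. For the foramen, "the diameter of the neuroforamen will be measured on sagittal CT reconstructions". For fat, the investigators developed a "grading scale based on the epidural fat reduction in the neuroforamen", with bands 0–25% (grade 1), 25–50% (grade 2) and 50–75% (grade 3). The top band, grade 4, is a reduction of more than 75%.

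**The concern.** Identifying patients who benefit more from one of the two operations is a stated aim (Background; Methods/design), and Table 3 is the list from which that search is made. Three features weaken it.

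1. Strict inequalities on both sides leave the boundary value without a group, so some patients would drop out of the age and Quetelet index analyses, or be assigned ad hoc.
2. Splitting a measured variable in two discards most of the variation within each half. Interaction tests usually have low power to begin with.
3. The foramen and fat items are not named as they are measured. A reader of Table 3 alone could take high grade to mean much fat, whereas on the defined scale it means much fat lost.

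At stake is the sensitivity and clear reporting of explorative analyses, not the trial's main conclusion.

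**Working it through.** The plan gives no figure to reproduce here. The check sets the texts side by side and then sizes the effect under stated assumptions.

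**Boundary values**

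- Age: the two groups are below 40 and above 40, so 40 is in neither. The eligible range of 18 to 70 holds 70 − 18 + 1 = 53 whole-year ages. If these were uniform (assumption), the share aged exactly 40 is 1/53 = 1.9%, and 220/53 = 4.2, about 4 of 220 patients.
- Quetelet index: the groups are below 25 and above 25, so 25 is in neither. The article gives no distribution. Assuming a normal distribution with mean 26 and SD 3 to 5, a recorded value of exactly 25 would apply to about 2 to 3 of 220 patients if the index is recorded to 0.1, and to about 17 to 28 of 220 if it is rounded to whole units.
- Fat bands: a reading of 25% fits grades 1 and 2, and a reading of 50% fits grades 2 and 3. At 75% there is no overlap, because grade 4 is "more than 75% fat reduction (grade 4", so exactly 75% is grade 3.

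**Information kept by a split**

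For a standard normal marker with a linear interaction, a cut at c keeps the fraction φ(c)² / [Φ(c){1 − Φ(c)}] of the information in the continuous marker. At the median, c = 0:

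- φ(0)² = 1/(2π), and Φ(0){1 − Φ(0)} = 1/4
- fraction = 4/(2π) = 2/π = 0.637

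The Sample size section gives 220 patients including 10% loss to follow-up, so 220 × 0.90 = 198 are evaluable. Then 0.637 × 198 = 126. For a normal marker the median is the most favourable single cut, so a cut elsewhere keeps less.

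**Labels**

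| Table 3 | Radiological examinations section | Difference |
|---|---|---|
| Cross section of the neuroforamen | Diameter on sagittal CT | Two terms for foraminal size |
| Grade of epidural fat | Grade of fat reduction, 1 to 4 | A higher grade means less fat |

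**The case against.** The case against is strong on several points, and most of it stands.

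- **Status.** The Table 3 analyses are called explorative. The primary comparison, the sample size and the two a priori subgroups do not depend on these items. This stands and limits the point to an optional improvement.
- **Unstated cut-offs.** A reader might infer that the splits of disc height, foraminal size and fat grade will be chosen after the outcomes are seen. The article does not say so, and it condenses a fuller protocol and perhaps an analysis plan, where such cut-offs commonly sit. Their absence here is not an error.
- **A marker that cannot be produced.** A reader might infer that the foraminal subgroup is impossible because an area cannot be derived from one diameter. Table 3 does not say area, and the diameter can be read as the size measure behind the small-versus-large contrast. CT is also planned for all patients before surgery. What remains is inconsistent wording.
- **A reversed subgroup.** A reader might infer that the fat subgroup is analysed the wrong way round. The article defines only one fat scale, and that definition settles the direction. Swapping the labels of a two-group split changes the sign of the interaction but not its p-value. What remains is an ambiguous label.
- **The 64% figure.** It describes a normal marker split at its median. Neither 40 nor 25 is stated to be a median, and fat reduction is a four-level scale. If the treatment effect really changed in a step at the chosen cut, the split would lose nothing. The figure is therefore illustrative. It also does not extend to items that are categorical as listed, such as sex, smoking or slip grade.

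The objection does not remove the unassigned values at 40 and 25, the shared band limits, the two mismatched labels, or the general loss from splitting a graded variable.

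**Conclusion.** The point holds as a low-cost improvement to explorative analyses. Age and Quetelet index are split so that the boundary value has no group. This affects about 4 of 220 patients for age if whole-year ages are uniform, and for Quetelet index a number that depends on rounding and on an assumed distribution. Two-group splits of measured variables give up information. Under normality, linearity and a median split, about 64% is kept, equivalent to 126 of 198 evaluable patients. The foramen and fat labels need to be reconciled with the section on radiological examinations, and the fat bands overlap at 25% and 50%. Nothing here touches the primary comparison, the sample size or the a priori subgroups.

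**What to change.** 1. Test the interactions with age, Quetelet index, disc height and foraminal diameter as continuous terms, and with fat-reduction grade as an ordinal term scored 1 to 4. Each uses one degree of freedom, as the two-group split does. Accompany each with a plot to check linearity.
2. Keep two-group splits for display only, with one side closed: <40 versus ≥40 years, and Quetelet index <25 versus ≥25.
3. In Table 3, use the measurement section's term, diameter, for the foraminal item, and rename the fat item *grade of epidural fat reduction*.
4. Make the bands non-overlapping, for example 0–25%, >25–50%, >50–75% and >75%.

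The cost is a change of wording in Table 3, the Statistical analysis section and the section on radiological examinations. The same images and baseline data serve, and neither sample size nor conduct changes. The one real downside is that a linear interaction is assumed, so a threshold or U-shaped pattern could be missed by the test. The plot is there to reveal it.

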## Discussion

In this article, the rational and design of a RCT on cost-effectiveness of two surgical strategies for sciatica caused by low-grade spondylolytic spondylolisthesis are described. To our knowledge this is the first RCT comparing nerve root decompression according to Gill versus instrumented spondylodesis. Based on the literature, the clinical results of nerve root decompression alone and instrumented spondylodesis seem equivalent, although solid conclusions cannot be made because of various methodological flaws.

The Sciatica-Gill trial is designed to elucidate the controversy in best surgical treatment of patients with symptomatic spondylolytic spondylolisthesis grade I and II. Gill's procedure is a less invasive procedure, patients can return to work quickly and instrumented related complications are avoided. However, secondary instrumented spondylodesis might be necessary in patients with persistent or recurrent leg pain. Currently, most surgeons advocate primary instrumented fusion. Arguments in favour of intercorporal spondylodesis are prevention of progressive slippage, enlargement of the neuroforamen, reduction of dynamic nerve root compression due to instability, and possible influence of low back pain. Whether more invasive surgery with higher costs and complications warrants instrumented spondylodesis as primary treatment, can be debated. Therefore we postulate that nerve root decompression according to Gill is more (cost-) effective on the short term and equally (cost-) effective on the long term, compared to instrumented spondylodesis. Subgroup analysis might identify patient groups who will benefit more from one of the treatments. The inclusion period will run until medio 2010 and follow-up measurements will be completed in 2012.

## Abbreviations

RCT: Randomised Controlled Trial; VAS: Visual Analogue Scale; CRF: Case Record Form; RDQ: Roland Disability Questionnaire.
